**Fig. 3 Fig3:**
[figure not shown]
Original power simulations of test offer (**A**), test acceptance (**B**), completion (**C**), and hepatitis C (HCV) antibody positive prevalence (**D**). Each point from each panel represents 1000 Monte Carlo simulated trials of total randomized patient visits with all other assumptions held constant

Accounting for the multi-site nature of the trial, and using preliminary data from a similar trial of HIV screening in EDs [25], we estimate the intra-cluster correlation (ICC) to range from 0.005 to 0.01, resulting in a design effect of 1.01–1.03, or a required 1–3% inflation of the sample size. Given the small number of clusters (3 sites) and the relatively large number of patients enrolled at each site, we anticipate the effect of clustering to be negligible; as such, we did not specifically modify the sample size for clustering but will account for it in the primary analysis. Finally, enrollment is planned to perform equal numbers of HCV tests across sites, resulting in a minimum of 16,667 randomized patient visits per site.

#### Screening Trial—blinded sample size re-estimation

In early April 2021, this trial crossed the 50% enrollment target and the final site, the University of Mississippi Medical Center, initiated enrollment. While performing general surveillance and trial monitoring, several assumptions used for the original sample size estimation were identified as being different from what was being observed during actual trial performance (Table 3). As such, a blinded sample size re-estimation (SSR) was undertaken using Monte Carlo simulation in SAS [26].

**Table 3 Tab3:** Original assumptions used to estimate sample size and weighted and inverse probability weighted estimates from observed trial performance through April 27, 2021, and 58.6% of target enrollment

	**Nontargeted screening**			**Targeted screening**		
	**Original assumptions**	**Weighted estimates**	**IPW estimates**	**Original assumptions**	**Weighted estimates**	**IPW estimates**
	**%**	**%**	**%**	**%**	**%**	**%**
**Test offer**	100	93.8	82.6	33	36.1	33.0
**Test accept**	60	26.4	33.0	60	34.0	47.0
**Test complete**	70	62.9	56.9	70	69.3	65.2
		**HCV testing**				
		**Original assumptions**	**Aggregate weighted estimates**	**Aggregate IPW estimates**	**Original assumptions**	
		**%**	**%**	**%**	**%**	
**HCV Ab+**		5	5.9	4.7	10	
**HCV RNA+**^a^		65	42.4	31.1	65	

*Abbreviations: HCV* Hepatitis C, *IPW* Inverse probability weighted

^a^Proportion of those who test HCV Ab+

As of April 27, 2021, the Screening Trial was at 58.6% enrolled and using these updated enrollment data, we project randomizing 129,663 visits across the three sites to complete 13,965 HCV antibody tests, as originally estimated. This increase in number of visits randomized reflects a 2.6-fold increase over the number originally estimated to be randomized (i.e., 50,000). Moreover, test acceptance (i.e., actual: 26% for nontargeted and 34% for targeted vs original: 60%) and RNA+ prevalence were significantly lower than originally estimated (i.e., actual: 42% vs original: 65%). Thus, we performed a series of additional simulations using methods described below to estimate the power to test the primary study hypothesis (Tables S1 and S2). Using both weighted and inverse probability weighted estimates to account for individual site contributions to total tests offered, tests accepted, and tests completed by study arm, while also using a two-way data table (Table S3) to model potential combinations of Ab+ prevalences by study arm using known aggregate Ab+ prevalence (and assuming RNA+ prevalence would not differ by study arm), we performed a series of additional simulations to estimate the power to test the primary study hypothesis.

Simulations using original assumptions and the originally planned 50,000 randomized visits, which the trial has already exceeded, resulted in significantly fewer total tests performed (*n* = 5,969) and power of only 0.3% (weighted and inverse probability weighted). Using the projected 129,663 randomized visits, estimates from current trial enrollment, and our original hypothesized effect estimate (i.e., RR = 1.25), simulations resulted in trials with totals of 15,452–15,623 (weighted) or 16,602–16,616 (inverse probability weighted) HCV Ab tests performed (exceeding our original estimation), while achieving powers of 65.7% (weighted) and 42.9% (inverse probability weighted). Fixing the RR at 1.25, simulations of 10% increased sample sizes (N = 142,629) resulted in  powers of 70.7% (weighted) and 43.0% (inverse probability weighted). Simulations of 30% increased sample sizes (N = 168,562) resulted in powers of 73.9% (weighted) and 52.8% (inverse probability weighted). Simulations of 50% increased sample sizes (N = 194,495) resulted in powers of 79.8% (weighted) and 57.7% (inverse probability weighted). Simulations with 129,663 randomized visits with varying Ab+ prevalences by study arm, constrained by the aggregate Ab+ prevalences (5.9%, weighted; 4.7% inverse probability weighted) and their respective 95% lower confidence limits (LCLs) (5.1% and 3.3%, respectively), resulted in RRs of 1.35 (weighted) and 1.45 (inverse probability weighted) to achieve a power >80% (Figs. 4 and 5). Given the steep slope of the power curve between simulated trials of 0% and 100%, it was noted that small changes in the Ab+ prevalence difference would result in relatively large changes in trial power. As such, the decision was made to not change the planned enrollment target from the original calculations.

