**Methods:**

The DETECT Hep C Screening Trial is a multi-center prospective pragmatic randomized two-arm parallel-group superiority trial to test the comparative effectiveness of nontargeted and targeted HCV screening in the ED with a primary hypothesis that nontargeted screening is superior to targeted screening when identifying newly diagnosed HCV. This trial will be performed in the EDs at Denver Health Medical Center (Denver, CO), Johns Hopkins Hospital (Baltimore, MD), and the University of Mississippi Medical Center (Jackson, MS), sites representing approximately 225,000 annual adult visits, and designed using the PRECIS-2 framework for pragmatic trials. When complete, we will have enrolled a minimum of 125,000 randomized patient visits and have performed 13,965 HCV tests. In Denver, the Screening Trial will serve as a conduit for a distinct randomized comparative effectiveness trial to evaluate linkage-to-HCV care strategies. All sites will further contribute to embedded observational studies to assess cost effectiveness, disparities, and social determinants of health in screening, linkage-to-care, and treatment for HCV.

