### Trial design

For this trial, we will perform a multi-center prospective pragmatic randomized two-arm parallel-group superiority trial, comparing two HCV screening strategies in the ED (Fig. 2). Allocation will be balanced using a 1:1 patient visit-level random allocation scheme built into the electronic health systems (EHSs) for each ED.

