### Statistical methods

After cleaning and locking the dataset, the primary analysis will be performed using the intention-to-treat principle while blinded to allocation. Continuous data will be reported as medians with interquartile ranges (IQRs) and categorical data as counts, proportions, and/or percentages with 95% confidence intervals (CIs). Bivariate statistical tests (e.g., Wilcoxon rank-sum test, Fisher’s exact test, etc.) will be used to compare variables between study groups. Patient-level data will be reported for all patient-level variables (e.g., age, sex/gender, race, ethnicity), although the primary unit of analysis will be patient visits. No interim analyses are planned given the pragmatic trial approach and minimal risk to subjects. Given the randomized design, the primary comparison will include an unadjusted RR for newly-identified HCV patients (primary outcome) with 95% CIs, specifically comparing nontargeted HCV screening to targeted HCV screening (primary hypothesis), while using a random effect hierarchical model to account for institution-level clustering, if present [26–28]. Sensitivity analyses will be performed to account for patients who were identified as Ab+ but RNA-, and subsequently determined to have been previously treated for HCV. Secondary comparisons will include all other outcomes by study arm, stratified by age, sex/gender, race, ethnicity, and institution. Statistical significance for the primary analysis will be defined as *p* <0.05 based on two-tailed statistical testing, which includes a lower 95% confidence limit of the RR >1.0. Although we do not anticipate significant missing data, multiple imputation will be used in instances where variables have >5% missingness. Although no formal interim analyses are planned for this trial, the study team may perform preliminary analyses for purposes of presentation at scientific meetings; these instances, if they occur, will be explicitly qualified as such and described as preliminary.

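### The re-estimated powers of 65.7% and 42.9% assume about 12% and 19% more HCV tests than the retained 13,965-test target; at that target power is about 55–61% and 35–37%

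*Protocol article*

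**What the plan says.** All of this is in the Protocol article. Under the blinded sample size re-estimation, the updated enrolment data give this projection: "we project randomizing 129,663 visits across the three sites to complete 13,965 HCV antibody tests, as originally estimated". The next paragraph uses the same number of visits with estimates from current enrolment, and reports that "simulations resulted in trials with totals of 15,452–15,623 (weighted) or 16,602–16,616 (inverse probability weighted) HCV Ab tests performed", noting that this exceeds the original estimate. The powers follow: "while achieving powers of 65.7% (weighted) and 42.9% (inverse probability weighted"). Larger trials of 142,629, 168,562 and 194,495 visits are given weighted powers of 70.7%, 73.9% and 79.8%.

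The section also gives RRs of 1.35 (weighted) and 1.45 (IPW) as those needed for more than 80% power at 129,663 visits. It ties them both to the aggregate antibody prevalences (5.9% and 4.7%) and to their lower 95% limits (5.1% and 3.3%). It closes by saying that "the decision was made to not change the planned enrollment target from the original calculations". The abstract states the end of enrolment as follows: "we will have enrolled a minimum of 125,000 randomized patient visits and have performed 13,965 HCV tests".

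**The concern.** One number of visits is tied to two test counts, and both are said to rest on observed enrolment. The power statement uses the larger count, while the target that was kept is the smaller one. The only power attached to 13,965 tests is the original figure of more than 80%, whose assumptions Table 3 replaces.

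If the trial stops at 13,965 tests, its power at RR 1.25 is lower than any figure the re-estimation reports for the planned enrolment. A null result would then be read against a power the trial did not have. The detectable RRs matter for the same reason, because the decision to keep the target is argued from how steeply power changes with the prevalence difference between arms.

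**Working it through.** **Inputs.** Table 3 gives offer, acceptance and completion by arm. Weighted: 93.8%, 26.4%, 62.9% (nontargeted) and 36.1%, 34.0%, 69.3% (targeted). IPW: 82.6%, 33.0%, 56.9% and 33.0%, 47.0%, 65.2%. Aggregate antibody prevalence is 5.9% or 4.7%, and RNA positivity among antibody positives is 42.4% or 31.1%. Allocation is a "1:1 patient visit-level random allocation scheme". Significance is "defined as *p* <0.05 based on two-tailed statistical testing, which includes a lower 95% confidence limit of the RR >1.0". The effect is RR 1.25.

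**Step 1: the plan's test counts.** Tests per visit are the mean over arms of offer × acceptance × completion.
- Weighted: (0.15576 + 0.08506)/2 = 0.12041; × 129,663 = 15,613.
- IPW: (0.15510 + 0.10112)/2 = 0.12811; × 129,663 = 16,611.

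Both agree with the simulated totals. The projection of 13,965 tests implies 13,965/129,663 = 10.8% of visits, against 12.0% and 12.8% here. The ratios are 15,613/13,965 = 1.12 and 16,611/13,965 = 1.19.

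**Step 2: the plan's powers.** Expected diagnoses D = tests × antibody prevalence × RNA positivity. With equal arms and a rare outcome, power ≈ Φ[(RR − 1)/(RR + 1) × √D − 1.96]. At RR 1.25 the multiplier is 0.25/2.25 = 0.1111.

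| Visits | D (weighted) | Weighted power, direct | Stated |
|---|---|---|---|
| 129,663 | 390.6 | 59% | 65.7% |
| 142,629 | 429.6 | 63% | 70.7% |
| 168,562 | 507.7 | 71% | 73.9% |
| 194,495 | 585.9 | 77% | 79.8% |

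For IPW at 129,663 visits, D = 242.8 and power is 41%, against 42.9% stated. That is reproduced within 2 points. The weighted figures are not reproduced: direct calculation is 3 to 7 points lower at all four sizes, with a Monte Carlo standard error of about 1.5 points or less for 1,000 runs. A 200,000-run binomial simulation with a Wald test on the log RR agrees with the direct figures (59.3% weighted, 41.0% IPW at 129,663 visits).

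**Step 3: power at 13,965 tests.**
- Direct, weighted: D = 13,965 × 0.059 × 0.424 = 349; Φ(0.1111 × 18.69 − 1.96) = 55%.
- Direct, IPW: D = 13,965 × 0.047 × 0.311 = 204; Φ(0.1111 × 14.29 − 1.96) = 35%.
- Scaling the stated weighted power: Φ[(1.96 + 0.404) × √(13,965/15,613) − 1.96] = 61%.
- Scaling the stated IPW power: Φ[(1.96 − 0.179) × √(13,965/16,611) − 1.96] = 37%.

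Like for like, the loss from fewer tests is 59% to 55% or 65.7% to 61% (weighted), and 41% to 35% or 42.9% to 37% (IPW). That is about 5 points, or up to 6 for IPW.

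**Step 4: visits against tests.** At Table 3 rates, 13,965 tests are reached at 13,965/0.12041 ≈ 116,000 visits (weighted) or 13,965/0.12811 ≈ 109,000 (IPW), both below 125,000. Conversely, 125,000 visits give about 15,050 or 16,010 tests, D ≈ 376 or 234, and direct power of about 58% or 40%.

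**Step 5: detectable RR at 129,663 visits.** For 80% power, (RR − 1)/(RR + 1) = 2.80/√D.
- Aggregate prevalence: D = 390.6 gives RR 1.33 (weighted); D = 242.8 gives 1.44 (IPW). The stated 1.35 and 1.45 are adequate.
- Lower limits: D = 15,613 × 0.051 × 0.424 = 338 gives RR 1.36 (weighted); D = 16,611 × 0.033 × 0.311 = 170 gives about 1.55 (IPW).

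The weighted gap is trivial; the IPW gap is not.

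**The case against.** The article is open about low power. It reports that the trial falls short at RR 1.25, that even 194,495 visits do not reach 80%, and that the target is kept regardless. A reader of a null result is already warned, and about 5 further points would change no stated decision. This stands as a limit on the seriousness of the point, but it does not make the printed powers apply to the retained target.

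Four stronger readings are tempting, and the document does not support them.
- *The shortfall in tests lowers weighted power from 65.7% to 55%.* This mixes two things. About 5 points come from the tests; the other 6 or so are the gap between the stated power and direct calculation at the plan's own test count.
- *The weighted powers are wrong.* The arm-specific prevalences came from a two-way grid in Table S3, with results in Tables S1 and S2, none of which is shown. A grid need not land exactly on RR 1.25, and an RR of about 1.27 would give 65.7%. The gap is a reason to recheck, not proof of error.
- *The end points conflict and leave the team free to choose when to stop.* The 129,663 visits are a projection. Enrolment stood at 58.6% when 50,000 visits had already been passed, and the monitoring section projects enrolment from tests performed, so progress appears to be counted in tests. The abstract's two conditions can be met together.
- *The article still claims more than 80% power and 611 diagnoses.* Those figures are under the original sample size estimation and are labelled as such.

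On the detectable RRs, the captions of Figures 4 and 5 name only the aggregate prevalences, where 1.35 and 1.45 hold. The figures are not shown. The text nevertheless attaches the same RRs to the lower limits.

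**Conclusion.** The point holds as a mismatch between the stated power and the retained target. The two test counts for 129,663 visits cannot both follow from the same completion rates, and the article does not reconcile them. If enrolment ends at 13,965 tests, power at RR 1.25 is about 55–61% (weighted) or 35–37% (IPW). The lower end is direct calculation and the upper end takes the stated powers as correct. If the 125,000-visit minimum also binds and Table 3 rates persist, direct calculation gives about 58% or 40%, so the loss is smaller. The IPW detectable RR of 1.45 does not cover the 3.3% lower limit.

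These figures assume Table 3 rates to the end of enrolment, equal RNA positivity in both arms (as the article assumes), a two-sided 5% test and no allowance for clustering by site. The test-count mismatch is certain from the text. The weighted-power discrepancy is unresolved without the supplementary tables.

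**What to change.** - Reconcile the projection of 13,965 tests with the simulated 15,452–16,616 tests for the same 129,663 visits, and say which completion rate is current.
- State whether enrolment ends on tests, on visits, or when both minimums are met.
- For that end point, give power at RR 1.25, expected diagnoses and detectable RR under the updated rates. For 13,965 tests, direct calculation gives about 55% and 35% power, 349 and 204 diagnoses, and RRs of about 1.35 and 1.49 for 80% power (weighted and IPW).
- Limit the RRs of 1.35 and 1.45 to the aggregate prevalences, and give separate values for the lower limits.
- Recheck the four weighted powers against the simulation output, and report the RR actually simulated if it was not exactly 1.25.

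The cost is some recalculation and less favourable printed figures. The design, the analysis and the number of patients do not change.

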**Fig. 4 Fig4:**
[figure not shown]
Sample size re-estimations using 1000 Monte Carlo simulations using weighted enrollment estimates and aggregate antibody positive (Ab+) of 5.9% to estimate power by Ab+ difference between nontargeted and targeted hepatitis C (HCV) screening

**Fig. 5 Fig5:**
[figure not shown]
Sample size re-estimations using 1000 Monte Carlo simulations using inverse probability weighted enrollment estimates and aggregate antibody positive (Ab+) of 4.7% to estimate power by Ab+ difference between nontargeted and targeted hepatitis C (HCV) screening

### Data collection methods

We will collect the following data for all eligible patients: (1) patient ED visit information (unique patient identifier, acuity level, mode of arrival, date/time of the visit); (2) demographics (age, gender, race, ethnicity, preferred language); (3) payer information (commercial, Medicare, Medicaid, self, or state assistance program); (4) details of randomization, including the intervention assigned and results of risk screening, if applicable; (5) whether a patient was offered, accepted, and completed rapid HCV testing; (6) results from all HCV Ab and RNA testing, if completed; (7) whether patients with detectable HCV RNA levels were successfully linked into care; and (8) components of the HCV care continuum. Data from (1) through (6) will be collected prospectively using methods developed by our team from each institution’s electronic screening, patient tracking, and laboratory reporting systems. We have long-standing and extensive experience interfacing with such systems across different institutions and obtaining large amounts of valid patient-level data [25]. Data from (7) and (8) will be retrospectively obtained using trained personnel and structured procedures.

As part of a sub-study to estimate risk among a representative sample of patients randomized to nontargeted screening, research assistants we will conduct surveys, using an electronic closed-response data collection instrument (REDCap, Vanderbilt University, TN), of patients enrolled into this specific study arm. No data or specimens will be collected for the current study or for future evaluation, including storage of biological specimens for genetic or molecular analyses.

### Data management

Denver Health will serve as the Data Coordinating Center (DCC) and data from non-Denver institutions will be transferred to the DCC using a Secure File Transfer Protocol (SFTP). Data will be extracted from each institution’s EHS and cleaned so that variables are consistent across sites. The cleaned and de-identified dataset will be sent via SFTP to the DCC for final data concatenation, cleaning, and analyses, performed using the most current version of SAS (SAS Institute, Inc., Cary, NC) (Figure S2).

### Statistical methods

After cleaning and locking the dataset, the primary analysis will be performed using the intention-to-treat principle while blinded to allocation. Continuous data will be reported as medians with interquartile ranges (IQRs) and categorical data as counts, proportions, and/or percentages with 95% confidence intervals (CIs). Bivariate statistical tests (e.g., Wilcoxon rank-sum test, Fisher’s exact test, etc.) will be used to compare variables between study groups. Patient-level data will be reported for all patient-level variables (e.g., age, sex/gender, race, ethnicity), although the primary unit of analysis will be patient visits. No interim analyses are planned given the pragmatic trial approach and minimal risk to subjects. Given the randomized design, the primary comparison will include an unadjusted RR for newly-identified HCV patients (primary outcome) with 95% CIs, specifically comparing nontargeted HCV screening to targeted HCV screening (primary hypothesis), while using a random effect hierarchical model to account for institution-level clustering, if present [26–28]. Sensitivity analyses will be performed to account for patients who were identified as Ab+ but RNA-, and subsequently determined to have been previously treated for HCV. Secondary comparisons will include all other outcomes by study arm, stratified by age, sex/gender, race, ethnicity, and institution. Statistical significance for the primary analysis will be defined as *p* <0.05 based on two-tailed statistical testing, which includes a lower 95% confidence limit of the RR >1.0. Although we do not anticipate significant missing data, multiple imputation will be used in instances where variables have >5% missingness. Although no formal interim analyses are planned for this trial, the study team may perform preliminary analyses for purposes of presentation at scientific meetings; these instances, if they occur, will be explicitly qualified as such and described as preliminary.

### Trial and data monitoring

In accordance with guidelines from the National Institutes of Health (NIH) and the primary funding agency, the National Institute on Drug Abuse (NIDA), we have developed a Data and Safety Monitoring (DSM) plan, and the principal investigators and core Denver-based research team will maintain appropriate oversight and monitoring of the trial’s conduct in its entirety, but in conjunction with site investigators. As this trial was not a phase 3 trial and that it was determined to be minimal risk to participants, no Data Safety Monitoring Board (DSMB) was required. The DSM plan was approved by the Colorado Multiple Institutional Review Board (COMIRB) and NIDA prior to initiating enrollment.

Data monitoring will be performed from the inception of participant enrollment at each site using data extracted from the EHS and transferred to the DCC using SFTP. The data manager will organize all data to understand total patient visits; inclusion and exclusion criteria; performance of Best Practice Advisories (BPAs) in Epic that were developed to facilitate enrollment and HCV screening; reasons for nursing actions related to BPAs; numbers related to HCV test offer, acceptance, and test completion by study arm; and aggregated test Ab and RNA results to ensure blinding. At the outset of enrollment, monitoring will occur nearly every day to ensure appropriate processes are occurring and to help guide trial performance. As our understanding of performance stabilizes, monitoring will be scaled back to a minimum of once weekly with frequent communication between the coordinating center and each site. Enrollment figures (e.g., modified CONSORT flow diagram, stacked bar graphs of enrollment by week of enrollment, stacked bar graphs of tests performed by study arm by week of enrollment, projected enrollment based on numbers of tests performed and estimated numbers of patients randomized, and trends of test acceptance by study arm) will be used to inform the study team’s understanding of trial performance and to inform any needed modifications while enrollment is occurring (Sample Monitoring Figures, Supplemental Appendix).

